## Abstract

**Background:**

Anomalous aortic origin of a coronary artery (AAOCA) is a rare congenital heart disease, potentially leading to myocardial ischemia and adverse cardiac events. As the sole presence of AAOCA does not always imply a revascularization, a detailed anatomical and functional analysis is crucial for clinical decision-making. Currently, invasive coronary angiography is the gold-standard method for a thorough hemodynamic assessment of AAOCA. However, due to its invasive nature, the development of noninvasive diagnostic alternatives is desired.

**Methods:**

In the NARCO trial, patients with AAOCA will undergo coronary computed tomography angiography (CCTA) to assess anatomical high-risk features followed by a vessel-based (i.e. invasive measurement with fractional flow reserve and intravascular imaging under a dobutamine-volume challenge) and a myocardium-based (i.e. nuclear imaging) ischemia testing. Comparison of noninvasive and invasive imaging will be performed. Additionally, explorative analysis of post-processing advanced computational fluid dynamics (CFD) and 3D printing will be performed to unravel the pathophysiologic mechanism of myocardial ischemia in AAOCA.

**Aims:**

Our primary aim is to define characteristics of anatomical high-risk features (using CCTA) to rule out noninvasively hemodynamically relevant anomalous vessels in AAOCA patients. The secondary aim is to investigate the underlying pathophysiology of AAOCA-related hemodynamic relevance using advanced techniques such as CFD and 3D printing.

**Conclusions:**

The NARCO trial will help to optimize AAOCA patient selection for revascularization by improving risk stratification and ruling out hemodynamic relevance noninvasively and, therefore, preventing unnecessary downstream testing and/or costly interventions in patients with AAOCA.

## Introduction

1

Anomalous aortic origin of a coronary artery (AAOCA) is a rare congenital heart anomaly that arises during embryonic development, stemming from abnormal integration of the initially formed subepicardial vascular plexus into the aortic root [1,2]. Conversely to other coronary artery anomalies (such as absent left main stem with two separate ostia for left anterior descending coronary artery and circumflex coronary artery), which do not present any clinical significance [3], AAOCA has been associated with a higher risk for myocardial ischemia and sudden cardiac death (SCD) [4]. Of particular interest are AAOCA with an intramural course (i.e. within the tunica media of the aortic root) [5], as this entity demonstrates a unique pathomechanism of myocardial ischemia with not only fixed stenotic components (similar to atherosclerotic lesions), but often the additional presence of dynamic stenotic components, based on lateral compression of the intramural segment during physical stress [6]. Besides the intramural course, further considered anatomical high-risk features are a slit-like ostium, an acute take-off angle, proximal narrowing of the anomalous segment, as well as a vessel deformation (i.e. an elliptic vessel shape). The sole presence of AAOCA itself or the additional feature of interarterial course (historically called malignant) is not per se an anatomic high-risk feature but rather a surrogate marker for other high-risk features (i.e. intramural course [5]). As the clinical presentation of AAOCA is very heterogeneous and the pathomechanism is complex, clinical decisions need to implement all information, and moving towards revascularization cannot solely rely on symptoms [7]. In fact, while most patients are asymptomatic, encountered symptoms may include many different forms, such as atypical chest discomfort, exercise-unrelated chest pain, dyspnea, dizziness, and palpitations, but as well more typical ischemic symptoms like angina pectoris, exercise-induced dyspnea, syncope, myocardial infarction and rarely SCD [6,[8], [9], [10], [11], [12]]. The latter has been particularly noted in young individuals and was closely associated with intense physical exertion according to autopsy studies [4,10,13]. Further, the current lack of evidence to inform practice guidelines [14,15] leads to ongoing uncertainty in risk assessment and selecting patients for revascularization [16,17]. In parallel, the increasing performance of guideline-conform coronary computed tomography angiography (CCTA) for the evaluation of stable chest pain syndrome [18], especially in the middle-aged and older population for coronary artery diseases assessment, leads to an increase of absolute numbers of coronary artery anomaly detection [5,[19], [20], [21]]. Due to the lack of evidence-based data, combined with the rising numbers of patients detected with AAOCA, the issue of improving clinical management of AAOCA is an urgent unmet need. Hence, we promote a thorough clinical work-up, including the determination of the hemodynamic relevance of the anomaly to make informed treatment decisions [6,22,23]. Invasive coronary angiography combined with intravascular imaging (intravascular ultrasound (IVUS), optical coherence tomography (OCT)) and pressure gradient measurement (fractional flow reserve [24], FFR) during a pharmacologic stress test is the preferred method for a comprehensive assessment, owing to its ability to evaluate the unique pathomechanism of myocardial ischemia in AAOCA. However, its invasive nature with the associated possibility of complications, as well as the uncomfortable rigorous pharmacologic stress test (i.e. dobutamine-volume challenge [6]) poses relevant limitations. Moreover, it represents a “vessel-based” rather than a “myocardium-based” assessment and, thus, neglecting additional physiologic factors contributing to patients’ overall AAOCA risk. Hence, there is a compelling need for a reliable, noninvasive diagnostic evaluation capable of comprehensively assessing the full clinical relevance of AAOCA.

### Pathophysiological mechanisms of myocardial ischemia in AAOCA

1.1

Guiding the clinical management requires a complete evaluation of the unique pathophysiology of myocardial ischemia in AAOCA. In contrast to the hemodynamic relevance in atherosclerotic coronary artery diseases (CAD), where a fixed reduction of the cross-sectional area causes flow restrictions and, thus, myocardial ischemia, an additional dynamic stenotic component becomes apparent in AAOCA [6].

For the evaluation of the fixed stenotic component, which shares similar pathophysiological characteristics with obstructive CAD, the same assessment tools can be utilized accordingly. Hence, measurement of the cross-sectional area reduction at the ostium (i.e. the slit-like ostium) respectively in the proximal part (i.e. proximal narrowing) in comparison to a distal “reference” diameter allows an evaluation of the fixed component. Additionally, an invasive measurement of the pressure gradient (i.e. FFR) along the anomalous segment, as implemented for the hemodynamic relevance of atherosclerotic lesions, can be applied [25]. Conversely, the dynamic stenotic component becomes only relevant in appearance under stress conditions. Even though the intramural coronary segment experiences a cyclical compression during systole (i.e. “phasic compression”), it usually does not impede diastolic coronary perfusion under normal resting conditions [9,26]. However, vigorous exercise with associated increased cardiac output, heart rate and elevated blood pressure results in an increased aortic wall stress. This, in turn, results in the expansion of the aortic diameter and an intensified lateral compression of the intramural coronary segment during both systole and diastole, thereby impeding diastolic coronary blood flow [6]. Additional exacerbating factors include the shortening of the diastolic phase as well as the aggravation of the acute-take-off angle and the elliptic vessel shape. Consequently, the dynamic stenotic component of hemodynamic relevance in certain AAOCA variants refers to a set of features that specifically emerge during intense physical exercise.

Importantly, the unpredictability of clinical ischemic episodes is influenced by additional factors like the patient's volume status, weight, body composition, heart rate and blood pressure, type of physical activity being performed, affected myocardial mass, and coronary dominance of the anomalous coronary artery, all contributing variably to potential impaired myocardial perfusion [27].

### Aims/Hypothesis

1.2

Our primary aim is to define characteristics/thresholds of anatomical high-risk features (using CCTA) to rule out noninvasively hemodynamically relevant anomalous vessels in AAOCA patients. An invasively measured FFR (under a dobutamine/volume challenge protocol) will serve as a reference standard to assess hemodynamic relevance. Based on this analysis, we want to implement a noninvasive CCTA-derived high-sensitivity rule-out test for the hemodynamic relevance of AAOCA.

Our primary hypothesis is that FFRdobutamine is associated with the extent and the individual combination of the anatomical high-risk features in patients with AAOCA. Patients will be grouped according to invasive FFRdobutamine (≤ or >0.80). Thus, hemodynamic non-relevant AAOCA with anatomical high-risk features will serve as controls. Assuming the validity of the hypothesis, the study result will allow patients to be deferred from unnecessary heart surgery, downstream testing, and/or sports restrictions.

Our secondary aim is to assess the performance of noninvasive myocardium-based ischemia testing (i.e. nuclear imaging) against vessel-based ischemia testing from invasive stress-evaluation. Further, we want to investigate the underlying pathophysiology of AAOCA-related hemodynamic relevance by using sophisticated, up-to-date computational fluid dynamics (CFD) techniques derived from CCTA and invasive data (in particular IVUS and FFRdobutamine). Analysis will be performed with non-commercially available research software to calculate FFR based on CT images (Siemens cFFR version 3.5.0 or higher Siemens Healthineers) [28], as well as with newly built CFD models with geometries based on CT images and combined CT/IVUS data [29]. All results will be validated against the invasively measured pressure measurements. Further, 3D printing flow-loop analysis will be explored. Last, all patients will undergo clinical follow-up. For the pursuing exploratory analysis, i.e. linking management and outcome to initial anatomical, ischemia testing, postoperative cardiac imaging, CFD and 3D printing models, retrospective as well as prospective data from the University Hospital of Bern registry and other external registries (e.g. University Hospital Zurich) are planned.

## Methods

2

Consecutive patients will be prospectively recruited from the established specialized clinic for coronary artery anomalies, Department of Cardiology, Inselspital, Bern University Hospital, Bern, Switzerland. All patients will, based on our established internal clinical guideline, undergo a CCTA with quantitative assessment of the anatomical high-risk features. After confirmation of the diagnosis, the patients will be included in the coronary artery anomaly NARCO registry (KEK 2020-00841, Clinical trials NCT04475289). For those with at least one anatomical high-risk feature (i.e. slit-like ostium, acute take-off angle, intramural course, proximal narrowing and/or elliptic vessel shape) an additional comprehensive diagnostic approach with a vessel-based ischemia testing using invasive FFR/IVUS under dobutamine and a myocardium-based ischemia testing (i.e. nuclear imaging, using physical stress or dobutamine stress) will be performed. Exams will be performed within a maximum of 6 months between the assessments. The following explanations will be focused on this subgroup of patients with a potential hemodynamic relevant coronary anomaly. Depending on the routinely acquired results of the invasive FFR and CCTA findings as well as the patients symptoms and individual risk factors (such as competitive sports activity), decisions regarding revascularization versus conservative treatment for the group of patients with a hemodynamically relevant anomaly will be made through an interdisciplinary approach involving interventional cardiologists, cardiovascular imagers, and cardiac surgeons. For the group of patients without evidence of hemodynamic relevance during the stress test and no AAOCA-suspected related persistence of symptoms, no further interventions (e.g. medical therapy and/or sport restriction) will be made. However, all patients will receive a follow-up within the NARCO-registry.

Lastly, CFD with reconstruction of the coronary artery circulation and fluid dynamic calculations will be continuously performed within the study duration without implication on the clinical management. Flowchart 1 graphically demonstrates the planned procedure. For secondary aims such as explorative anatomical, ischemia testing, as well as CFD and 3D printing models linked to management and clinical outcome data, not only prospective-, but also retrospective included patients from the coronary artery anomaly registry will be assessed.

**Fig. 1 fig1:**
[figure not shown]
Flowchart 1: Illustration of the study procedure

### Anatomical assessment

2.1

All subjects will undergo a routinely acquired CCTA imaging. Based on its excellent spatial resolution and advanced post-processing techniques enabling a detailed quantitative assessment of the anatomical high-risk features, CCTA is the preferred imaging modality in the adult population for the anatomical evaluation over magnetic resonance imaging and echocardiography [30]. Of particular interest is the vessel origin, vessel course [31,32] and quantitative assessment of the slit-like ostium (in %) [31], the exact take-off angle (in degrees) [31], the length of the intramural segment (in mm) [31,[33], [34], [35]], the proximal narrowing (also referred as proximal hypoplasia, in %) as well as the extent of vessel deformation (i.e. elliptic vessel shape, dimensionless ratio) [36]. Further, the take-off height (in mm) of the anomalous vessel will be analyzed [37].

### Functional assessment

2.2

#### Vessel-based ischemia testing

2.2.1

Patients will undergo left heart catheterization and coronary angiography for diagnostic purposes from the right radial artery approach. Biplane coronary angiography with perpendicular recording of the anomalous segment (required for post-processing analysis) will be performed. In cases with a significant coronary lesion downstream of the anomalous segment, percutaneous treatment will be performed before the study protocol. All patients receive a continuous infusion of saline (max. 3l) after assessment of the resting parameters as preparation for the dobutamine/volume challenge (Flowchart 2).

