**Fig. 2 fig2:**
[figure not shown]
Flowchart 2: Illustration of the study procedure during the vessel-based ischemia testing including the dobutamine/volume challenge

Following diagnostic coronary angiography, a 0.014 inch pressure monitoring angioplasty guidewire (PressureWire™ X Guidewire, Abbott, Chicago, Illinois, United States) will be calibrated and positioned in the distal part of the vessel downstream of the anomalous segment. Next, calculation of resting non-hyperemic pressure ratios (i.e. instantaneous wave-free ratio, resting full cycle ratio and Pd/Pa, all calculated as previously described [38,39]) will be performed. After recording the resting indexes, baseline (i.e. under resting condition) IVUS will be assessed at the site of maximal stenosis (minimal cross-sectional area). IVUS pullback will be conducted at a speed of 0.5 mm/s throughout the suspected lesion. Lesion length, oval-vessel shape and minimal cross-sectional area at rest and during pharmacologic stress will be assessed in the Bern University Hospital Corelab.

Further, FFRadenosine will be assessed during administration of intravenous (i.v.) adenosine (140 μg/kg/min for approximately 2min). FFR will be calculated as the ratio of mean distal (non‐ectopic coronary) pressure to mean aortic pressure and will be considered positive if FFR≤0.80 [40].

Last, dobutamine/volume challenge will be performed by administration of i.v. dobutamine at a rate of 20mcg/kg/min for 2 min, followed by 4 min of i.v. dobutamine at a rate of 40mcg/kg/min. In addition, up to 3 L of saline solution will be administered to counteract cardiac preload reduction and subsequent systemic blood pressure drop by dobutamine. If the maximal heart rate (=220-age) will not be reached after 6 min, 0.5–1 mg of intravenous atropine will be given aiming for the maximum tolerable heart rate. Throughout the stress test, aortic as well as distal coronary artery pressure will be recorded continuously for calculation of FFRdobutamine. At maximal achieved heart rate, the above mentioned IVUS protocol will be repeated for the assessment of the hyperemic values (i.e. evidence of a lateral compression). Afterward, dobutamine will be stopped, and esmolol (10 mg stepwise) will be given to slow down the heart rate.

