### Image post-processing

2.3

CFD will be performed with dedicated CFD coronary artery software and with general-purpose CFD models [29]. Dedicated CFD models are based on independent, non-commercially available onsite research software developed to estimate FFR from CCTA (cFFR by Siemens Healthineers) [28]. The software allows to calculation of FFR based on the patient's CCTA images after segmentation of the coronary tree. This dedicated CFD model uses fixed assumptions specific to coronary arteries and a simplified model instead of solving the full Navier-Stokes equation, only requiring the user to perform the segmentation of the coronary artery tree. Further analyses will be performed with the use of general-purpose CFD software (e.g. ANSYS 2022R2, Pennsylvania, USA). Lastly, three-dimensional models of the left and right coronary trees will be generated from coronary CTA images using proprietary, purpose-developed software (Mimics, Materialise, Leuven, Belgium) to segment coronary arteries and determine vessel centerlines.

Data from the invasive assessment will be used to validate results of the CFD analysis. The governing Navier–Stokes equations for the conservation of mass and momentum will be solved with the finite volume method (Fluent 14.5, ANSYS). Mean pressure distal to the interrogated lesion will be obtained from the blood flow simulation in the vessel location matching the invasive FFR measurement based on interpretation of the invasive coronary angiography images recording pressure wire position. Matching will be blinded to the invasive FFR measurement. FFRCT values will then be calculated by dividing the mean pressure distal to the coronary anomalous segment (identical to the invasive position) by the mean aortic pressure [44].

Additionally and as an exploratory analysis, we will create 3D models combined of segmented IVUS images and CCTA images [45,46]. These 3D printings will then be used to perform flow-loop analysis [47].

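### Where a downstream lesion is treated first, CT-derived FFR from the pre-treatment CCTA is validated against an FFR recorded after treatment

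*Protocol article*

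**What the plan says.** The relevant statements are spread over several sections of the protocol article.

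- **Order of tests.** The abstract says that "patients with AAOCA will undergo coronary computed tomography angiography (CCTA) to assess anatomical high-risk features followed by a vessel-based" and then a myocardium-based test. Section 2 (Methods) makes CCTA the entry test: "After confirmation of the diagnosis, the patients will be included in the coronary artery anomaly NARCO registry", and only patients with at least one high-risk feature go on to invasive and nuclear testing. On spacing it says "Exams will be performed within a maximum of 6 months between the assessments".
- **Treatment.** Section 2.2.1 (Vessel-based ischemia testing): "In cases with a significant coronary lesion downstream of the anomalous segment, percutaneous treatment will be performed before the study protocol".
- **Reference measurement.** Still in section 2.2.1, the wire comes next ("Following diagnostic coronary angiography, a 0.014 inch pressure monitoring angioplasty guidewire") and is "positioned in the distal part of the vessel downstream of the anomalous segment".
- **CT-derived FFR.** Section 2.3 (Image post-processing) calculates FFR from the patient's "CCTA images after segmentation of the coronary tree". For the flow simulation, the distal pressure is read "in the vessel location matching the invasive FFR measurement", with this matching blinded to the invasive value.
- **Comparisons.** Section 1.2 (Aims/Hypothesis) has all CFD results validated against the invasive pressures, and nuclear imaging assessed against the invasive stress test.

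**The concern.** A validation study assumes that index test and reference describe the same vessel in the same state. In a patient whose downstream lesion is treated before the FFR, the CCTA still contains that lesion and the FFR does not. Any difference between CT-derived and invasive FFR then mixes the error of the method with the effect of the treatment. The blinded location matching does not address this, because it fixes where the pressure is read and not which state of the vessel is modelled.

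At stake is the secondary aim: how well cFFR and CFD reproduce invasive FFR in AAOCA. The same problem would reach the nuclear comparison if a scan was taken before the treatment. A perfusion defect caused by the lesion could then be set against an FFR measured without it.

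**Working it through.** The plan gives no figure on this point to reproduce. The check consists of tracing the sequence and then sizing it.

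**Sequence for a patient with a treated downstream lesion**

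1. CCTA at entry: lesion present (abstract; section 2).
2. Percutaneous treatment before the invasive protocol (section 2.2.1).
3. Pressure wire in the distal vessel, then FFRadenosine and FFRdobutamine: lesion treated (section 2.2.1).
4. cFFR and CT-only CFD from the step 1 images: lesion present (section 2.3).
5. The step 4 result is compared with the step 3 pressure (section 1.2), matched on position only (section 2.3).

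Steps 4 and 5 therefore pair a pre-treatment geometry with a post-treatment reference. The article mentions no repeat CCTA, no modelling of the treated state and no separate handling of these pairs.

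**Which comparisons are reached**

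| Comparison | State of index test | State of FFR | Mismatch |
|---|---|---|---|
| cFFR, CT-only CFD | before treatment | after | yes, in treated patients |
| Combined CT/IVUS models | CT before, IVUS after | after | partial; depends on which segment IVUS replaces |
| Nuclear imaging | not known from the text | after | only if scanned before treatment |
| CCTA features of the anomalous segment (primary) | before | after | little: the features describe a segment upstream of the lesion |

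**Direction.** If the pressure is read beyond the lesion, the lesion in the model lowers CT-derived FFR relative to the invasive value. If it is read between the anomaly and the lesion, the lesion in the model reduces flow through the anomaly and would raise it. A distal wire makes the first case plausible, but the text does not settle it.

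**Size.** Planned number: 50, for the primary aim (section 2.4). The treated share is not given. With an assumed share s, the affected patients number 50 × s:

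- s = 2%: 1
- s = 5%: 2.5
- s = 10%: 5
- s = 20%: 10

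For scale, the article's figure of about 18% with FFR ≤0.80 gives 0.18 × 50 = 9 positives and 50 − 9 = 41 negatives. If all 50 entered the comparison, one FFR-negative pair read as positive because of the mismatch would move specificity by 1/41 = 2.4 percentage points. That is a ceiling per pair, since a mismatch need not carry the value across 0.80.

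**The case against.** The strongest case against the point has five parts.

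- **The primary aim is protected.** The primary features (ostium, take-off angle, intramural length, proximal narrowing, elliptic shape) belong to the anomalous segment, and treating a lesion further down does not change them. Treating first also helps FFRdobutamine reflect the anomaly. This stands. A reader might infer that a residual gradient in the treated vessel could push patients into the FFR ≤0.80 group and so damage the primary sensitivity. Nothing in the article says or implies that such a gradient remains.
- **Discordance is not guaranteed.** A reader might infer that CT-FFR must read falsely low in these patients. The mismatch of states follows from the text. Its direction, and whether it crosses 0.80, depend on lesion severity and wire position. This stands.
- **The nuclear mismatch is conditional.** The text gives no order for nuclear and invasive testing, but Flowchart 1 illustrates the procedure and is not shown, so a missing order cannot be held against the plan. The words about treating before the study protocol could also mean before all study testing. Nuclear imaging would then follow treatment, although the entry CCTA would ordinarily still precede it. This stands.
- **The affected group may be very small.** The rule covers only significant lesions downstream in the anomalous vessel, and CFD is described as explorative. This stands, and it limits the weight of the point.
- **Handling of such pairs belongs in an analysis plan.** The article is condensed, and the full protocol may deal with treated patients. This stands only in part. The point does not rest on silence: the stated sequence, the location-only matching and the validation of all results, applied as written, together produce the mismatched pairs.

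**Conclusion.** The point holds for the secondary comparison of cFFR and CT-only CFD with invasive FFR. For patients treated downstream before the invasive protocol, the plan as written pairs a pre-treatment geometry with a post-treatment reference, and the comparison can be biased for them. It holds for nuclear imaging only where the scan came before the treatment. It does not reach the primary comparison to any material extent.

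The size is uncertain. About 1 to 10 of 50 patients is an illustration at an assumed 2% to 20% treated, not an estimate from the documents. The 50 is the number for the primary aim, and the number entering the CFD comparison is not stated.

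The conclusion rests on two readings. One is that treatment takes place after the entry CCTA, which its place in the catheterization section supports. The other is that the entry CCTA is the scan used for modelling, with no repeat scan after treatment.

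**What to change.** Add one analysis rule, set before results are seen:

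- Flag every vessel treated between an index test and the invasive FFR.
- Leave such pairs out of the main cFFR/CFD-versus-FFR comparison, unless the index test was acquired in the same coronary state as the FFR.
- Do the same in the nuclear-versus-FFR comparison where the scan preceded the treatment.
- Report the excluded pairs in a sensitivity analysis, with their number.

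The text should also state which tests the phrase about treating before the study protocol refers to, so that sections 2, 2.2.1 and 2.3 can be read together.

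The cost is a flag, which the catheterization record should already supply, and a few pairs lost from secondary comparisons. Setting the rule in advance also avoids any later suspicion that discordant pairs were removed after the event. No change to patient care is proposed.
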